**Fig 2 pone.0284297.g002:**
[figure not shown]
Probable Long Covid definition for study inclusion.

*Stage 1 (reaching out)*. The study’s promotional material will use the criteria from the WHO Clinical Case Definition of Post COVID-19 condition to raise awareness for consideration of potential participants who may be experiencing Long Covid [3]. These include:

History of probable or confirmed (by rapid antigen or PCR testing) SARS-CoV-2 infection three months or more from the time of recruitmentProlonged symptoms after infection (a list of the 10 most common symptoms will be provided) lasting at least 2 months that cannot be explained by an alternative or previous diagnosisSymptoms have an impact on everyday functioning

Potential participants who think they fulfil the above criteria will be encouraged to contact the research team by phone or email. A member of the research team will go through a set of questions for stage 2 screening below.

The 10 most common symptoms highlighted: Exhaustion/fatigue, cognitive dysfunction (brain fog, memory problems, concentration problems, occasional confusion), breathlessness, headache, muscle aches, palpitations, chest tightness/pressure/pain, dizziness, sleep disturbance and joint pain.

*Stage 2 (screening criteria)*. A screening questionnaire will be administered by a member of the research team to check eligibility. The above three criteria will be checked first. To be specific, the potential participant will be asked whether they had confirmed or probable COVID-19 at least 3 months ago, whether than have experienced prolonged symptoms not explained by a pre-existing health condition for at least 2 months after infection, and whether these symptoms restrict or limit their daily activities.

If the answer is yes to all three, a question will be asked whether the potential participant has an existing clinical diagnosis of Long Covid. If the answer is no, further questions about specific symptoms and their pattern will be asked. Given the evidence that Long Covid is predominantly a multi-system condition [7], participants will be included if they have three or more of the symptoms listed below. The choice of three symptoms as a cut-off was made based on the evidence which points out that Long Covid is predominantly a multi-symptom and multisystem condition [7, 38, 39], and discussions with CAB.

Post-exertional symptom exacerbation (symptoms such as fatigue, difficulty thinking, pain recurring after remission or getting worse following exertion, either immediately or up to 72 hours post exertion) [40], exhaustion, cognitive dysfunction (brain fog, memory problems, concentration problems, occasional confusion), breathlessness, headache, muscle aches, palpitations, chest tightness/pressure, chest pain, dizziness, sleep disturbance, joint pain, leg pain, pins and needles feeling, tinnitus, sore throat, cough, nasal symptoms, hoarse voice, abdominal pain, nausea, diarrhoea, chills, altered or loss of sense of smell, altered or loss of sense of taste, skin rash, loss of appetite and sneezing.

The above screening process form the criteria for inclusion in the study rather than a tool upon which clinical decisions are made. Those who fulfil the stage 2 screening criteria will be assumed to have probable Long Covid and asked if they are interested to take part in the study.

Participants will be asked to read the Participant Information Sheet (PIS) in paper or digital format. A member of the research team can also read it to them, or they can watch a short video describing the study using the same information included in the PIS. If they are interested to take part, they will be asked to complete the study’s consent form (in paper or online version). Arabic, Somali and Bengali are three of the most spoken community languages in Camden [41]. If needed, Arabic, Somali, and Bengali versions of the PIS short video can be provided. Study documents can be translated into these community languages if this is required following an assessment of recruitment progress 6 weeks into the study. Some participants, especially those with additional needs or those who speak community languages, may prefer to have the documents read and/or explained to them by a friend, carer, or voluntary organisation worker. Whether they opt in the study or not, they will be directed to NHS resources and/or NHS 111 website for further information about the kind of help they can seek regarding their symptoms. Fig 3 shows the eligibility screening and participant flow chart.

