## Background

Long Covid is a patient-coined term, initially defined as not recovering from SARS-CoV-2 infection after at least 4 weeks from onset [1, 2]. The World Health Organization (WHO) defines post COVID-19 condition (also known as Long Covid) as the condition that occurs in those with probable or confirmed SARS-CoV-2 infection, usually three months from onset with symptoms and that last for at least two months, not explained by an alternative diagnosis and impacts everyday functioning [3]. The Office for National Statistics (ONS) estimated that as of June 2022, two million people are currently living with Long Covid in the UK [4] and around 12% of those who tested positive for COVID-19 up to August 2021 (including those initially asymptomatic) experience symptoms consistent with Long Covid for at least 12 weeks from infection [5]. Of those living with Long Covid, 72% experience limitations of their day-to-day activities, with 21% describing their day-to-day activities as ‘limited a lot’ by Long Covid [5]. It disproportionately affects people living in more deprived areas (as measured by the English Index of Multiple Deprivation, IMD [6]), those with another health condition or disability, and those in frontline professions, such as teachers, health care professionals and people working in social care [4].

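### The Stage 2 screening question is narrower than the Stage 1 criterion it says it checks, because it omits explanations that arose after the infection

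*Protocol article*

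**What the plan says.** All references are to the protocol article.

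- **Background.** The WHO definition is summarised as a condition "not explained by an alternative diagnosis and impacts everyday functioning".
- **Eligibility criteria, Stage 1 (reaching out).** The promotional material carries three criteria: infection at least three months earlier, symptoms for at least two months, and an effect on daily functioning. The symptom criterion rules out two kinds of explanation, an alternative diagnosis and a previous one.
- **Eligibility criteria, Stage 2 (screening criteria).** A member of the research team administers a questionnaire. The text says "The above three criteria will be checked first" and then specifies the questions. The symptom question asks about "prolonged symptoms not explained by a pre-existing health condition for at least 2 months after infection". Next come a question on an existing clinical diagnosis of Long Covid and questions on specific symptoms and their pattern. The final rule is that "participants will be included if they have three or more of the symptoms listed below".
- **Consequence.** Those who meet Stage 2 are taken to have probable Long Covid and are offered participation.
- **Symptom lists.** Stage 1 has "chest tightness/pressure/pain" as a single entry. Stage 2 has "chest tightness/pressure, chest pain" as two entries.

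**The concern.** Stage 1 is self-assessment from a leaflet or advert. Stage 2 is the step at which the research team decides who is a probable case. If the Stage 2 question omits part of the criterion, an interviewer who follows the text will not ask about that part.

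The first objective is to find probable cases who lack recognition and care. The listed outcomes include describing the people found, their barriers to care and the stigma they experience. Someone whose symptoms already have another established explanation may lack a Long Covid diagnosis for that reason rather than because of a barrier. Including such people without knowing it would blur the account of barriers that the interviews are meant to give.

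**Working it through.** The plan states no figure to reproduce on this point. The check compares the passages and then traces one hypothetical enquirer through the text.

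**1. The exclusion, source by source**

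| Source | Explained by a condition present before the infection | Explained by a condition that arose and was diagnosed since the infection |
|---|---|---|
| Background (WHO definition) | Ruled out, as an alternative diagnosis | Ruled out, as an alternative diagnosis |
| Stage 1 criterion | Ruled out, as a previous diagnosis | Ruled out, as an alternative diagnosis |
| Stage 2 question | Ruled out | **Not ruled out** |

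Only the last cell differs. A condition that predated the infection but was diagnosed afterwards is a borderline case under the Stage 2 wording. A condition that arose afterwards is clearly not covered.

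**2. One enquirer traced through Stage 2**

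Take an adult infected four months ago, with three months of limiting symptoms that a condition diagnosed since the infection explains.

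- Infection at least three months ago: yes.
- Symptoms for at least two months, not explained by a pre-existing condition: yes, truthfully.
- Daily activities restricted: yes.
- Existing clinical diagnosis of Long Covid: no.
- Three or more listed symptoms: yes, by assumption.

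The result is a probable case, although the Stage 1 criterion would rule this person out. No remaining Stage 2 step in the text asks about another diagnosis. After the interview, the Community care pathway section describes social prescribing, GP contact and possible clinic referral. It does not say that findings from these steps return to revise case status.

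**3. Weight of one misclassified person**

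The section on qualitative data collection expects 20 to 30 interviews.

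- 1 / 30 = 3.3% of the sample.
- 1 / 20 = 5.0% of the sample.

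The documents do not give the share of enquirers with a new alternative diagnosis, so no expected number can be calculated.

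**4. The chest item**

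The Stage 1 list has 10 symptoms and the Stage 2 list has 28. Someone with chest pressure and pain plus one other complaint has two symptoms on the Stage 1 grouping but three on the Stage 2 list, and so reaches the cut-off.

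- Possible sets of three from 28: 28 × 27 × 26 / 6 = 3,276.
- Sets containing both chest items: 26, one for each possible third item.
- Share: 26 / 3,276 = 0.8%.

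This is a share of combinations, not of participants, because the documents give no symptom frequencies. It shows only that the discrepancy is narrow.

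**The case against.** The best defence is that the exclusion has not been removed. The sentence just before the question says all three Stage 1 criteria are checked, and people make contact only if they think they meet those criteria. On this view the Stage 2 wording is a loose paraphrase in a condensed article. The questionnaire itself, Fig 2 (the probable-case definition) and Fig 3 (the flow chart) cannot be seen and may carry the full wording.

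Much of this stands. A reader might infer that the study abandoned the alternative-diagnosis exclusion; the text does not support that, and the fault is an inconsistency between adjacent statements. The defence does not remove the inconsistency, though. The narrower wording is introduced as the specific form of the check, and self-selection from a leaflet does not replace the team's own screening.

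It can also be said that this is a qualitative pilot with no prevalence or yield estimate among its listed outcomes, and that a later alternative label might itself reflect the dismissal the study wants to explore. Both points limit the consequence. Neither shows that the narrowing was intended, since the text says the full criteria apply.

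On symptom counting, a reader might infer that overlapping items let in people who fail the study's definition, or that the cut-off should require more than one body system. The documents support neither. The rule counts listed items, so two listed items count as two. The cut-off rests on evidence that "Long Covid is predominantly a multi-symptom and multisystem condition" and on Community Advisory Board discussions, and an item count serves the multi-symptom part directly. A reader might also infer that the counted symptoms need not be prolonged, but questions on symptom pattern are planned and their content is not shown.

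**Conclusion.** The point holds as an internal contradiction in the eligibility text. Followed as written, the deciding screen can admit people whom Stage 1 and the cited WHO definition rule out. The conflict is shown between the Background, Stage 1 and Stage 2 texts only; whether Fig 2 and the questionnaire share it cannot be told. The conclusion takes pre-existing in its ordinary sense, as present before the infection.

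The size is modest. Each affected interviewee is 3.3% to 5.0% of the planned sample, and the number affected is unknown. No sample-size, power or error-rate figure is involved. The chest-item mismatch is a minor secondary inconsistency and does not make any included person fail the stated rule. The correction is worth making because it is simple, but the point does not threaten the study as a whole.

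**What to change.** Reconcile the two stages by wording the Stage 2 question to match Stage 1. For example, ask whether the symptoms have lasted at least two months after the infection and are not explained by any alternative or previous diagnosis, whether made before or since the infection. Check that Fig 2, the flow chart and the screening questionnaire say the same.

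At the same time, align the two symptom lists so that chest tightness, pressure and pain are grouped the same way in both.

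The cost is a change of questionnaire wording and, where needed, a minor amendment. The downside is that a few enquirers whose symptoms are otherwise explained will not be enrolled.

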**Fig 3 pone.0284297.g003:**
[figure not shown]
Eligibility and screening flow chart.

*What happens after cases have been identified and they have consented to take part?*

#### Qualitative research data collection

Participants will be invited to take part in a qualitative semi-structured interview conducted by a member of the research team. The qualitative interview will explore participants’ awareness of Long Covid and symptoms, their experiences of trying to access care and the barriers they may experience when trying to access care as well as stigma and perceived discrimination by asking broad, open questions. Example questions within the interviews: ‘Please can you tell me a bit about your experience of Long Covid?’; ‘How comfortable have you felt seeking Long Covid care?’ ‘How have you tried to seek Long Covid treatment or care’; ‘What do you think could make it easier for people to access Long Covid care?’; ‘what do you think there is anything (outside of health care) that could make it easier for people living with Long Covid?’ Prompts may sometimes be used to encourage participants to give more full descriptions of their experiences. Prompts will include reference to: symptoms and whether these have been relapsing and/or episodic in nature [7, 38]; different forms of care/support sought; barriers and perceived discrimination when accessing care; and different forms of support. Self-reported demographic data will also be collected within the semi-structured interviews.

Stigma questions within the topic guide are based on a validated Long Covid stigma scale [22] based on health stigma theory, emerging qualitative evidence of Long Covid stigma and stigma questions used for other conditions such as HIV and myalgic encephalomyelitis. The semi-structured nature of the interviews means that the research team use a topic guide to inform the areas to discuss during the interview. There is no expectation to rigidly follow any order of questions instead it is a guide of areas of interest with open questions about experience and opinions with some prompts for the interview of specific areas of particular relevance to the research questions. The researcher will be able to adapt the interview to fit each participant, depending on the participant’s answers. Participants will also be asked for feedback on the pilot’s promotional material that they have accessed and input on what is important for them to see in future educational material on Long Covid.

Interviews will take place via video call, telephone or face-to-face. Participants who are unable to complete the interview via these formats will be able sent a written version of the topic guide and invited to write their own responses and add additional areas relevant and important to them. Interviews will take around 45–90 minutes to complete, depending on the participants’ answers. It is expected that 20–30 interviews within 9 months will need to be completed before data saturation occurs, or when information and/or themes begin to be repeated within interviews. Some participants may prefer a friend, carer, or voluntary organisation representative to be present to make the process easier for them. Participants can also request for interpreters, for both community language speakers and British Sign Language (BSL) users, to be present at interviews. Interviews will be recorded and then transcribed by a professional transcription service. Once an interview has been transcribed, the digital recording will be deleted. Transcripts will be stored securely on university servers.

Thematic analysis will then be used to analyse the transcripts. Thematic analysis will be based on the approach set out by Braun and Clarke [42]. This approach involves becoming familiar with the interview transcripts, creating codes based on participants’ responses and in relation to the research questions, creating themes that emerge from the transcripts and checking and revising these themes (if necessary) before writing the results [42]. This analysis will be aided by NVivo 12 qualitative analysis software.

#### Outcomes

The measures of success and key outcomes of this pilot study will be:

Co-produced appropriate Long Covid educational/awareness materials that have received input during the pilotDescribed characteristics of people identified within this pilot who are not accessing careDescribed the barriers to accessing care and the stigma experienced by people living with Long CovidPiloted a personalised referral/support pathway as part of service deliveryDeveloped components of health professional training based on the findings of this active case finding to enhance understanding of the experiences of people living with Long CovidAdvising local organisations on Long Covid plans that are locally specific

#### Research participation reimbursement

Participants who complete the qualitative interview will be offered a paper or online shopping voucher as a gesture of recognition for their time. This decision was based on CAB members unanimously agreeing that a financial incentive would be necessary to show gratitude to participants who take part in interviews. The research team do not believe that any ethical issues will arise from offering this voucher incentive; the monetary value of the voucher is too low to be considered coercive [43] The intention behind the payment offer is to show that the participants’ time and effort are valued.

#### Community care pathway

During our CAB discussions, accessing Long Covid clinics/services was challenged as the only end goal for most people living with Long Covid. CAB members suggested that although improving health outcomes is a priority, individuals with Long Covid may need help solving other problems, such as debt or housing issues, too. A personalised, person-centred, approach will be piloted in service provision, including clinical and non-clinical pathways and social support based on identified needs of individuals living with Long Covid. The feasibility of a multi-pronged community-based service approach will be explored by our local partners as described below.

VAC is an ‘umbrella’ organisation that links with and supports other voluntary organisations in the Camden area [44]. VAC works with the North Central London (NCL) Care Commissioning Group (CCG) and Age UK Camden to provide The Care Navigation and Social Prescribing Service in the local area [37, 44]. Residents in Camden can self-refer for the local social prescribing service, but referrals also come from health services [37, 44]. VAC have recently began receiving referrals from the University College Hospital (UCLH) post-covid clinic as part of a pilot pathway to see if social prescribing can have a positive impact on patients living with Long Covid.

Social prescribing will be incorporated into the pilot at the Camden site. Once the qualitative interview has been completed, consent will be sought from the participant to refer them to VAC social prescribing team (if they have not accessed the study through signposting from VAC already). Social prescribers will speak with the participant if they consent and develop a person-centred approach to provide support that is meaningful to them. This might be a healthcare-focused approach but social prescribers can also make referrals to different organisations such as debt help, help with budgeting and peer support, amongst others [37]. As some participants will be recruited through signposting from VAC, it is likely that some participants may have these conversations with social prescribers prior to contact with the research team. This element will be part of routine local service delivery rather than research.

Social prescribers will be able to send a referral through to University College Hospital (UCLH) Post-Covid service if necessary. The participant will be advised to contact their primary care provider to discuss their symptoms and consider a clinical assessment and/or an e-referral to the post-covid service through the electronic system if deemed appropriate by their GP. Following consent of participants, the study team can also provide a letter for the participant to forward to their GP once the qualitative interview is completed if requested by the participant. If the social prescribing team is involved, they may also contact the GP as part of service provision if advocacy is required. Social prescribers will also be able to refer patients to the Camden Borough level Multi-disciplinary Team (MDT) to be put on their meeting schedule if deemed appropriate.

All identified cases will also be provided with a list of local support organisations. If the need for more urgent referral is needed, the participant will be strongly encouraged to promptly contact their GP or NHS 111 as appropriate.

### Ethics and risk management

This pilot forms part of the NIHR-funded STIMULATE-ICP study [45]. This includes three work-packages. This protocol refers to work under work-package 3a. Work-package 2 of STIMULATE-ICP is a pragmatic cluster randomised trial (IRAS project ID 1004698) [23]. WP1 and WP3 are the observational elements (IRAS project ID 303958) [24]. Participants for this pilot will be recruited from the community not the NHS and therefore NHS IRAS/REC approval was not sought for this element. The active case finding study protocol and related study documentation have received ethical approval from the University of Southampton Ethics Committee and the Research Integrity and Governance team (reference number 72400). Informed consent will be obtained from all participants prior to their participation in this pilot study.

## Publication and dissemination

Findings will be reported in a report and submitted for peer-reviewed publication. Definitive methods of dissemination will be decided by the CAB. Summaries of the findings will also be shared on the STIMULATE-ICP website, locally in the study area and through social media. We will specifically target policy makers and those responsible for shaping and commissioning Long Covid healthcare services and social support. Anonymous data will be available upon request, conditional on relevant ethical and research governance approval.

